## Abstract

**Background:**

Broadly disseminating and implementing evidence-based psychotherapies with high fidelity, particularly cognitive behavioral therapy (CBT), has proved challenging for many health-care systems, including the Department of Veterans Affairs, especially in primary care settings such as small or remote clinics. A computer-based tool (based on the coordinated anxiety learning and management (CALM) program) was designed to support primary care-based mental health providers in delivering CBT. The objectives of this study are to modify the CALM tool to meet the needs of mental health clinicians in veterans affairs (VA) community-based outpatient clinics (CBOCs) and rural "veterans", use external facilitation to implement CBT and determine the effect of the CALM tool versus a manualized version of CALM to improve fidelity to the CBT treatment model, and conduct a needs assessment to understand how best to support future implementation of the CALM tool in routine care.

**Methods/design:**

Focus groups will inform the redesign of the CALM tool. Mental health providers at regional VA CBOCs; CBT experts; VA experts in implementation of evidence-based mental health practices; and veterans with generalized anxiety disorder, panic disorder, social anxiety disorder, posttraumatic stress disorder, "with or without" depression will be recruited. A hybrid type III design will be used to examine the effect of receiving CBT training plus either the CALM tool or a manual version of CALM on treatment fidelity. External facilitation will be used as the overarching strategy to implement both CBT delivery methods. Data will also be collected on symptoms of the targeted disorders. To help prepare for the future implementation of the CALM tool in VA CBOCs, we will perform an implementation need assessment with mental health providers participating in the clinical trial and their CBOC directors.

**Discussion:**

This project will help inform strategies for delivering CBT with high fidelity in VA CBOCs to veterans with anxiety disorders and PTSD with or without depression. If successful, results of this study could be used to inform a national rollout of the CALM tool in VA CBOCs including providing recommendations for optimizing the adoption and sustained use of the computerized CALM tool among mental health providers in this setting.

**Trial registration:**

ClinicalTrials.gov, NCT02488551

## Background

Multiple randomized controlled trials (RCTs) have demonstrated that evidence-based psychotherapies (EBPs), particularly cognitive behavioral therapy (CBT) [1, 2], are highly effective for treating anxiety and depression, the most common mental health disorders in primary care settings [3–5]. The Department of Veterans Affairs (VA) has made it a national care priority to increase the availability and accessibility of EBPs across all VA medical facilities and clinics, to Veterans needing mental health care [6].

However, broadly disseminating and implementing (a process often referred to as “scaling up”) these and other EBPs has been a challenge in many health-care systems [7], including the VA [8, 9]. While training of clinicians is needed for scaling up, training alone is inadequate to assure that EBPs are not only implemented but also implemented with enough fidelity to optimize their clinical effectiveness [10]. Without adequate implementation and fidelity, patients realize few benefits and the resources devoted to training clinicians fail to improve patient outcomes.

Implementing EBPs in small or remote primary care clinics, such as many VA community-based outpatient clinics (CBOCs), can be especially challenging. A 2008 study showed that only 22 % of veterans with depression, anxiety, or posttraumatic stress disorder (PTSD) received at least one session of psychotherapy and rural veterans were even less likely than urban veterans to receive any psychotherapy [11]. Furthermore, the quality of the psychotherapy received in these settings is unknown. Mental health providers in CBOCs, many of which are located in rural and highly rural areas, are often the only mental health provider at the clinic and may be isolated from their peers and from educational resources. Further, some of these providers have been trained in specific EBPs [6] but may not have the resources or time needed to become proficient in these skills. Therefore, efforts to implement tools to support and assist CBOC mental health providers in delivering EBPs with high fidelity are needed.

The National Institute of Mental Health-Funded Coordinated Anxiety Learning and Management (CALM) study [12–14] faced a similar challenge in implementing CBT in 17 non-VA primary care clinics across the USA with providers, usually nurses and social workers, most of whom had no previous training or experience in CBT. To meet this challenge, researchers developed a computer-based tool to support primary care-based mental health providers in delivering CBT to patients with a range of disorders, including panic disorder (PD), generalized anxiety disorder (GAD), social anxiety disorder (SAD), PTSD, and comorbid depression [15].

### CALM program

The CALM program, including the computer and manual versions, was created to guide and train mental health providers in using CBT. The computerized CALM tool was not intended, like some other computer-based psychotherapy tools [16, 17], as a self-help intervention (i.e., patient facing without provider involvement). The CALM tool involves the patient and provider looking at the computer screen together and proceeding through the modules at their own pace [15]. Continuous use of this tool in treatment may have the added benefit of helping to maintain fidelity to the CBT treatment model. The CALM CBT tool is unique in that it can be used to treat anxiety disorders (PD, GAD, SAD), PTSD, and comorbid depression. This is accomplished through the use of basic CBT modules that are commonly employed across these disorders plus additional, branching modules that are disorder-specific [13]. In one study, the CALM tool, used by 13 providers in treating more than 250 patients in a variety of primary care clinics, was found to be acceptable to providers and patients and resulted in substantial treatment engagement and homework compliance [15]. Most importantly, the CALM tool is clinically effective (relative to standard care) [12] for all disorders (PTSD, PD, GAD, SAD with or without depression) [13]. Furthermore, the improved clinical outcomes achieved in CALM appear to be due primarily to receipt of CBT delivered with this computer program [12]. A tool providing fidelity support to mental health providers who are social workers, nurses, masters’ level counselors, and psychologists in primary care could help support VA CBOCs providers in delivering CBT and also improve outcomes.

### Implementation strategies and study aims

Implementing CBT in large health-care systems such as the VA is a substantial challenge [18] as barriers to implementation tend to vary at the site and provider levels. Initial training in EBPs typically is not sufficient for promoting its sustained use, with researchers suggesting a need for more intensive facilitation to address barriers to promote the use of a new practice in a “real-world” setting [18]. Facilitation is a key component of the promoting action on research implementation in health services framework, which specifies the potential roles of a facilitator in promoting the adoption of new clinical practices [19, 20]. For example, external facilitation can be used to address site- and provider-specific implementation barriers by using a facilitator who understands the complexities of the specific health-care system and who works with clinical teams to address implementation challenges as they arise [10, 21–23]. Facilitators use problem-solving, provide interpersonal support, and function as mentors to clinical teams to support the adoption and sustained use of a new practice [21]. In one study, external facilitation was used in ten VA clinics to implement CBT and was associated with a larger increase (19 %) in the use of CBT from baseline when compared to ten VA clinics (4 %) not receiving facilitation [21]. Together, these findings suggest that external facilitation is a key component to promoting the adoption of EBPs, and especially in large health-care settings where barriers to implementation can be numerous and vary across clinics and providers.

### Current study

The goal of this article is to describe our study, which involves four aims: to (a) modify the CALM tool to meet the needs of CBOC mental health providers and rural veterans; (b) use external facilitation to implement two CBT delivery methods (CALM tool versus CALM manual); (c) determine the effects of these two delivery methods to improve fidelity to the CBT treatment model; and (d) conduct a needs assessment to understand how best to support the future implementation of the CALM tool in routine VA care. A hybrid type III study design was chosen to allow for a primary focus on comparing two implementation strategies or delivery methods (CALM tool or CALM manual) of CBT and also collect patient-level outcome data. We will examine the effect of these tool delivery methods on CBT treatment fidelity (primary outcome). External facilitation will be used as an overarching implementation strategy to support the adoption of both methods for delivering CBT. Our secondary outcomes include patient-level data on reductions in anxiety and depressive symptoms among veteran patients over time in both conditions. Collecting patient-level outcomes will fill an important gap in CALM treatment outcome literature by providing data on the clinical effectiveness of CALM for veteran patients receiving care in VA CBOCs.

## Methods/design

The following section(s) describe the three study aims and hypotheses, study participants, data collection, and analysis plans that will be used to achieve each aim. Human subject approval for aim 1 of this study was granted by the Central Arkansas Veterans Healthcare System Research Committee. Aims 2 and 3 were approved by the Veterans Affairs Central Institutional Review Board.

### Aim 1: modify the CALM tool

We used methods common to the field of instructional design and technology to guide the redesign of the CALM computer tool for use in VA CBOCs. Instructional design and technology is a field of study that provides a systematic process for applying human and media resources to efficiently accomplish instructional goals [24]. The wide variety of instructional design and technology models described in the literature [25–27] share the core elements of analysis, design, development, implementation, and evaluation. These core elements are applied in an iterative and formative process. While these methods were originally designed to develop instructional materials, they are well suited for developing and refining online therapeutic-didactic tools and are consistent with formative evaluation methods commonly used in implementation research [10, 28].

*Analysis* typically includes inquiry about the audience or end user, the potential goals of the training/program, and the context in which the training/program will occur. *Design* (or *redesign* in the present study) is typically concerned with identifying goals and objectives for content (e.g., changing some treatment vignettes to reflect veterans and their perspectives and requirements for reading level) and a plan for “look and feel” (e.g., web presentation, toolbars, color scheme). *Development* refers to the construction of the prototype materials (e.g., the web tool with videos, all navigation working). *Implementation* refers to the process of putting the product into practical effect, i.e., when the content is posted to the web and the target audience uses it. *Evaluation* is seen as a continuous formative activity throughout the process. We hypothesize that the modified CALM tool will be acceptable to CBOC mental health providers and veterans.

### Study participants

We aim to collect qualitative data from four stakeholder groups: (a) CBOC mental health providers; (b) veterans who have an anxiety disorder or PTSD with or without depression.; (c) expert CBT clinicians; and (d) experts in the implementation of EBPs within the VA (Table 1). Feedback from CBOC mental health providers will help ensure that the content is presented in a way that is acceptable to them, that clinical vignettes and case studies presented are realistic, and that the navigation and flow of the material meets their clinical needs. Providers will be recruited from CBOCs located in the south central VA region of care encompassing Oklahoma and east of Texas to the Florida panhandle and Arkansas to the Gulf of Mexico. Feedback from veterans, recruited from this same region of CBOCs, will help ensure that the CBT material is acceptable to the target audience of patients; the case examples are reflective of their experience and that homework assignments are understandable and feasible to complete. Feedback from CBT experts, recruited from VA and non-VA locations, will help ensure that the empirical support underlying the tool is not compromised. Feedback from VA implementation experts will help the research team create the facilitation strategies to be used at the CBOCs. These strategies will support implementation of both the CBT delivery methods, as both will need facilitation to support training of the providers and their participation in continuing consultation for CBT.

**Table 1 Tab1:** Participant eligibility criteria for each study aim

Study aim	Participants	Eligibility criteria
Aim 1: modify the CALM tool	Mental health providers (*n* = 8)	Inclusion criteria -works in a VISN 16 CBOC
	Veterans (*n* = 8)	Inclusion criteria -diagnosed with GAD, PD, SAD, and PTSD with or without depression within the last year -had at least two mental health visits at a VISN 16 CBOC in the prior year
	CBT experts (*n* = 4)	Inclusion criteria -VA or non-VA are eligible
	- Experts in the implementation of EBPs within VA (*n* = 4)	Inclusion criteria -VA employee involved in national “rollouts” of EBPs
Aim 2: hybrid type III effectiveness-implementation study	- Mental health providers (*n* = 34)	Inclusion criteria: -willing to receive a 3-day CBT training -has an office with a computer -willing to be audiotaped and participate in clinical supervision -willing to be randomized to CALM tool or manual version of CALM
	Veterans (*n* = 340)	Inclusion criteria: -patient of a participating provider -plan to continue to receive mental health care -diagnosed with PD, SAD, GAD, or PTSD with or without depression -want to receive CBT -willing to have therapy sessions audiotaped -willing to participate in clinical assessments Exclusion criteria: -no evidence of a significant cognitive impairment -not actively suicidal -no comorbid substance use disorders, schizophrenia, or bipolar disorder -not completed a course of CBT or cognitive processing therapy
Aim 3: implementation needs assessment	Mental health providers (*n* = 34)	Inclusion criteria: -must have participated in aim 2 -CBOCs with mental health providers participating in aim 2
	- CBOC directors	

### Data collection

All data will be collected in focus groups. Focus groups are a standard method in “new product development” and are widely used by marketing researchers to get feedback on new and existing products [29]. Focus groups provide a flexible mechanism for gaining insight into how others think, and they provide an efficient mechanism for understanding a range of diverse opinions at a meaningful level of detail [30]. One focus group will be created for each of the four stakeholder groups. Each focus group will meet at least three times to provide iterative feedback on the redesign of the CALM tool (via the analysis, design, development, implementation, and evaluation model). The first focus group will review the existing CALM tool and provide recommendations on revisions and new elements, the second will review the initial design plans and storyboards (“mock ups”) for the revisions and new elements, and the third focus group will review the prototype tool in a live web demonstration with a test clinician and test patient. The third focus group will have the opportunity to observe the CALM tool operating exactly as it will during the study trial.

The focus groups for the stakeholder groups (except veterans) will occur by teleconference with the assistance of Lync, an online meeting portal that allows participants to view the same material online simultaneously. Participants are able to leave written comments and feedback in the “chat room” as well as provide verbal feedback on the phone. The veteran focus groups will be in-person to limit potential barriers (access to teleconference software) to participating. Focus groups will be conducted by two individuals—one with expertise in the CALM tool and one with expertise in eliciting qualitative feedback. The group leaders will use interview guides that are helpful in keeping the interviews “on track” and minimizing the possibility that the interviews will be completed without “covering” topics that the study team feels are important to discuss [31]. Use of a guide, however, will not limit the interviewers from asking new questions or following participants along new lines of inquiry [32].

### Data analysis

To quickly produce the information needed to revise the CALM tool, we will use rapid data analytic techniques informed by Sobo et al. [33, 34]. Two notetakers will listen to audio recordings of the focus groups (and document recommended modifications provided in the chat room function of the online meeting portal) and summarize the feedback and recommendations from each focus group. They will resolve any differences that might have arisen from their separate note-taking. The notetakers will present their summaries to the focus group leaders and collectively finalize the feedback summaries from each group. The feedback summaries from each focus group will be used to develop a document listing categories (e.g., content, look and feel) that will be used to revise the CALM tool. For example, the first set of summaries will be provided after the focus groups view and respond to the current tool. A second set of summaries (or more if needed) will be provided after the focus groups view and respond to the design plans and draft storyboards of revisions. A third set of summaries (or more if needed) will be provided after the prototype has been reviewed and tested.

### Prototype development

The research team and the instructional/web design team that developed the original version of the CALM tool will work together to develop the redesigned version of the CALM computer tool. Possible modifications may include revising the language used to present the material, updating the graphics and images, and developing new instructional video clips with actors portraying veteran patients and veteran-specific scenarios.

### Aim 2: hybrid type III study

Our second aim we will be to use a hybrid type III [35] study design to conduct an RCT comparing the effect of a modified CALM tool versus that of a manualized version of CALM on our primary outcome—CBOC mental health provider fidelity to CBT. A hybrid III study design was used given (a) a substantial and clear evidence base indicating improved clinical outcomes associated with patients receiving CALM; (b) a strong need to identify optimal delivery methods for implementing CBT in VA CBOCs; and (c) the fact that CALM has significant “implementation momentum” [35] as our VA Central Office research partners are interested in adapting the CALM tool for use in VA CBOCs. Mental health providers will be randomized to receive CBT training plus the CALM tool or a manualized version of CALM. We hypothesize that providers randomized to receive CBT training and the CALM tool will demonstrate higher treatment fidelity than providers receiving the manual. We also hypothesize that veteran patients of providers randomized to receive CBT training and the CALM tool will have clinical outcomes superior to veteran patients of providers who receive the manual.

### Study participants

Participants will include mental health providers and veteran patients. We will recruit 34 mental health providers (all disciplines eligible) to receive training in CBT. Upon completion of training, each mental health provider will invite ten of his/her patients to participate in CBT treatment (Table 1).

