### Training and consultation

All providers will receive training in CBT. The training will be of the same length and format (3-day, face-to-face) as initial training programs in VA rollouts of EBPs [37]. The training will differ across the two groups (those randomized to receive the CALM tool versus manual) in that the final 2 h of each day will involve practice with either delivery method. All providers who complete the training (regardless of randomization) will receive consultation for 3 months, which will consist of small group discussion with “audit and feedback” reports to therapists. Consultation will focus on coaching and giving providers feedback on the delivery of CBT. Both elements have been shown to be important in ensuring proficient delivery of EBPs [38]. Providers will audiotape all of their clinical sessions, and the consultant will review a sample of audiotapes from their sessions during the first 3 months. The consultant will review all recordings from the providers’ first patient and will provide written (via e-mail) or oral (via telephone) feedback after the second and last sessions. If a provider appears to need additional instruction, the supervisor will provide weekly individual consultation over the telephone for the provider until both agree that any problems have been resolved.

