#### Fidelity ratings

Fidelity assessments will focus on therapy sessions delivered early and late in the project. Fidelity for the first patient will be assessed and used to control for initial group differences in multivariate analyses. We expect each therapist to see ten patients each, with each patient completing up to eight sessions. Fidelity will be assessed only for patients who have attended at least four sessions. Fidelity will be measured for a “midpoint” patient (patient four or five of ten) and the last patient receiving at least four treatment sessions from each therapist. Fidelity for the midpoint and last patient for each therapist is our primary outcome measure. A single overall fidelity rating will be completed for each (midpoint and last) patient’s last three sessions. A minimum of 5 % of the total sessions being analyzed will be randomly selected to be rated by both raters to characterize inter-rater reliability.

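### Patients are recruited after allocation by providers who know their arm, which leaves the clinical-outcome comparison open to recruitment bias

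*Protocol article*

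**What the plan says.** The order of events can be read directly from the protocol article.

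- **Randomisation** (Aim 2: hybrid type III study): "Mental health providers will be randomized to receive CBT training plus the CALM tool or a manualized version of CALM". The provider is the randomised unit; patients are not randomised.
- **Training** (Training and consultation): the arms differ in that "the final 2 h of each day will involve practice with either delivery method". The allocation is therefore known to every provider by the end of training.
- **Recruitment** (Study participants, Aim 2): "Upon completion of training, each mental health provider will invite ten of his/her patients to participate in CBT treatment".
- **Eligibility** (Table 1): the veteran criteria are general and begin "patient of a participating provider -plan to continue to receive mental health care". Some depend on willingness, for example "want to receive CBT -willing to have therapy sessions audiotaped".
- **Fidelity** (Fidelity ratings): "Fidelity for the midpoint and last patient for each therapist is our primary outcome measure", with the restriction that "Fidelity will be assessed only for patients who have attended at least four sessions".
- **Analysis** (Data analysis, Aim 2): the covariates described are provider characteristics. Mental health functioning is measured at baseline, 3 and 6 months.

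**The concern.** In a trial that randomises providers, randomisation makes the providers comparable in expectation. It makes their patients comparable only if recruitment takes place before allocation is known, or in a way that allocation cannot influence. Here recruitment follows allocation and is done by someone who knows it.

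The article hypothesises better clinical outcomes among patients of tool providers, and that comparison needs similar patients in the two arms. Differences could arise without any intent. The tool is used with patient and provider looking at a screen together, so a tool provider might think first of patients who are at ease with a computer. Patients' willingness to take part may also depend on which format they are offered. A difference in prognosis that arose in this way would be read as an effect of the delivery method.

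Fidelity is less exposed. It is a behaviour of the randomised unit, but it is rated on only two patients per provider, the midpoint and the last, so case mix has little chance to average out.

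**Working it through.** **1. Do the passages allow the bias?**

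| Step | What the article states | Allocation known to the provider? |
|---|---|---|
| Randomisation | Providers assigned to tool or manual | Becomes known |
| Training | Arm-specific practice on each training day | Yes |
| Invitation | Ten of the provider's own patients, after training | Yes |
| Clinical baseline | Before CBT begins, on recruited patients | Yes |
| First-patient fidelity, used as an adjustment | After training, on a patient the provider invited | Yes |

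No step identifies patients before allocation or uses a recruiter unaware of the arm. Neither planned adjustment is measured before the patients are recruited. Both can reduce an imbalance that they capture, but neither can show that the recruited patients were comparable on traits that were not measured.

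**2. How much could it matter for the clinical outcome?**

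Inputs from the Power analysis section are n = 300 patients, ICC 0.10, 30 providers and therefore 10 patients each. The selection shift b is an assumption, because the documents give no value.

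- Design effect = 1 + (10 − 1) × 0.10 = 1.9; effective sample size = 300 / 1.9 = about 158.
- Standard error of the arm difference = √(4/300 × 1.9) = 0.159 SD.
- Check on the plan's own figure: for d = 0.5 the noncentrality is 0.5 / 0.159 = 3.14. On 28 degrees of freedom this gives 85.8 % power, in line with the stated 85 %. The standard error is therefore consistent with the one behind the plan.
- With no true effect and a shift b, the two-sided 5 % test on 28 degrees of freedom has noncentrality b / 0.159:

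| Assumed shift b (SD) | b / SE | False-positive rate, t on 28 df | Normal approximation |
|---|---|---|---|
| 0.1 | 0.63 | 9.3 % | 9.6 % |
| 0.2 | 1.26 | 22.9 % | 24.2 % |
| 0.3 | 1.88 | 44.4 % | 47.0 % |

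These rates assume that the whole shift survives into the analysis. If baseline adjustment removed half of a 0.2 SD shift, 0.1 SD would remain and the first row would apply (ignoring any gain in precision from the adjustment).

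**3. The same illustration for fidelity.**

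With 15 providers per arm and b in provider-level SD, the standard error is √(2/15) = 0.365. Shifts of 0.1, 0.2 and 0.3 give false-positive rates of 5.8 %, 8.3 % and 12.5 %. For equal assumed shifts the exposure is much smaller than for the clinical outcome.

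**The case against.** Several points can fairly be made against this.

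- **Provider discretion is not stated.** The article says that providers invite patients, not how the ten are identified. Free choice is the plain reading, but a full protocol could contain a selection rule, and an article commonly leaves such procedures out. This stands. The missing rule is not the finding by itself; the finding is the stated order, in which unmasked providers invite after allocation.
- **Bias needs selection that differs between arms.** Providers in both arms would have the same reason to invite patients who are easy to treat. If manual providers did so more, the bias would run against the study hypothesis. This stands, and it means that neither direction nor size can be derived from the text.
- **Fidelity belongs to the provider.** The rated patients are fixed by position, and the article does not say that order of invitation sets that position. A reader might infer that providers can steer which patients are rated, or that the primary result is biased. The documents do not support either inference. They allow only that case mix, together with the four-session condition, could have some effect.
- **Baseline is measured.** Clinical outcomes are framed as reductions over time, so an imbalance in baseline severity would be at least partly removed by an analysis of change or of baseline-adjusted scores. This stands for measured severity. It does not cover motivation, readiness for homework or comfort with computers.

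**Conclusion.** The concern holds for the secondary clinical outcomes. As described, patient recruitment is unmasked, follows allocation and is limited only by general eligibility criteria. The claim that patients of tool providers do better therefore does not have the full protection of randomisation. For the primary fidelity outcome the same route exists through case mix, but it is secondary and its direction is unknown.

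The rates of about 9 %, 23 % and 44 % illustrate assumed shifts of 0.1, 0.2 and 0.3 SD with no correction by baseline adjustment. They are not estimates of what will happen. It would go too far to read the article as showing that providers hand-pick patients or that the results will be biased: it shows that they can be, and it states no safeguard. The point is worth acting on. Confidence is moderate, because a full protocol might contain a selection rule.

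**What to change.** 1. Before allocation is disclosed, each provider submits a list of currently eligible patients.
2. Patients are invited in list order. When the list runs out, it is topped up only with strictly consecutive eligible patients; any looser rule would reopen the same route.
3. Eligible, invited, declined and enrolled patients are logged by arm and reported.
4. The secondary clinical model adjusts for the baseline score already collected, with a statement that this does not remove selection on unmeasured traits.

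**Cost.** One list per provider, a log, and a few sentences in the recruitment and analysis sections. It brings modest administrative work and possibly slower enrolment, and the lists may go stale for patients treated late. Self-selection remains, because patients must want CBT. Having study staff issue the invitations would strengthen the safeguard, but it needs extra resources across dispersed clinics and is best treated as optional. No additional patients are needed. The Study status section reports only Aim 1 recruitment under way, so at that point the Aim 2 procedure could still be changed.
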